Mindfulness facilitates the ability to shift attention to experiences purposefully, with a sense of acceptance (as opposed to trying to change or react to it).17 Active mechanisms of mindfulness (e.g., improved attention, emotion regulation, decentering)18-22 combined with the unique circumstances of HCT caregivers, suggest that approaching thoughts/emotions/sensations via mindfulness may convey benefits above and beyond what is found in other treatment approaches.23-25 Mindfulness has been associated with psychosocial benefits in other populations (e.g., decreased negative affect26-31 and stress32,33). To date, a few small-scale, single-arm studies have investigated mindfulness for the cancer patient-caregiver dyad with promising results.34-38 There have been no studies examining mindfulness for HCT cancer caregivers. Our multi-disciplinary team systematically developed a 6-week mindfulness-based intervention for allogeneic HCT caregivers – FOCUS (**F**ocusing **O**n mindfulness for **C**aregivers **U**nder **S**tress) – with input from caregivers and transplant team members. FOCUS spans the course of patient treatment, with session 1 occurring prior to transplant, sessions 2-3 taking place immediately following transplant, and sessions 4-6 occurring post-discharge. Pilot testing revealed that FOCUS was highly feasible and acceptable for allogeneic HCT caregivers and useful for managing stress.39 Significant decreases in negative affect and increases in mindfulness, post traumatic growth, and mental health symptoms were observed from baseline to end of treatment; findings were maintained through the 1-month follow-up.

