**Project Overview and Timeline**. Caregivers (N=270) will be randomized (1:1:1) to one of three study conditions: FOCUS, Healthy Living (HL), or Usual Care (UC). Both caregivers and patients will be assessed at baseline, end of treatment (~8 weeks post-baseline), and 2- and 6-months post-treatment. Figure 3 presents the study timeline for caregivers and patients, anchored by the day of the patient’s transplant (Day 0). Patients and caregivers will be recruited and consented about 2 weeks (~Day -14 to ~~ Day -10) prior to the patient’s scheduled transplant day. Patients are often in the clinic for vital organ testing in preparation for HCT at this time. The caregiver will then be randomized to FOCUS, HL, or UC. For FOCUS and HL, we plan for session 1 to occur the around week prior to transplant, session 2 the week of transplant, and session 3 the first week post-transplant. These sessions will be scheduled at the appointment that coincides with our timeline, but because there may be medically related changes in schedules (e.g., unanticipated complications), we will be flexible in the timeline for sessions. Sessions 4-6 will occur post-discharge, once the patient is released within a 30 minute radius of the cancer center (patients and caregivers typically stay within 30 minutes of the cancer center for the first 100 days post-transplant). Although this schedule will accommodate most patient/caregiver schedules, we expect some schedules to differ. For instance, some patients have their discharge around Day+18-22, if certain symptoms need to resolve. We encountered these issues during the pilot study and will flexibly accommodate such changes as they arise in the current study.

[figure not shown]
The end of treatment assessment will take place within approximately 1 week of session 6. Follow- up visits will occur about 2 months and 6 months post-

treatment. The 2- month follow-up time point will allow us to capture short- term treatment gains reported since the

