A subsample of patients will be asked to complete a telephone interview (approximately 30-45 minutes in length) in order to obtain feedback about the possibility of having patients engage in a stress management intervention in a future study. Approximately 30 patients whose caregivers were randomized to either the HL or FOCUS interventions will be asked to participate in the phone interviews at approximately the 2-4 month post EOT follow up period. Every other patient enrolled with a caregiver in one of those two conditions will be asked to participate in an individual phone interview. The number of patients asked to participate will be approximately 15 per caregiver’s condition (HL or FOCUS) or until saturation of feedback (i.e., no new information is offered by participants). Approximately 20 open ended questions will include queries about the patient’s emotional and physical experience around the transplant process, including the pre-hospitalization, hospitalization for transplant, and post-hospitalization periods. Specifically, stress, coping, stress management, and awareness of caregiver’s stress management program will be queried. Patients will also be asked for their thoughts about offering stress management to patients and what types of support would have been useful. Interviews will be recorded, transcribed, and coded for themes.

**Randomization.** Participants (caregiver/patient dyads) will be randomized at enrollment, to one of the three treatments using balanced-permuted blocks of size six toward assigning 90 dyads to each condition. Caregivers will be stratified by gender prior to randomization as research indicates male and female cancer caregivers differ on distress and coping styles.114

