|  | Distress | Thermometer | 1 | X | X | X | X |  |  |
|  | COVID | created | 5 | X | X | X | X |  |  |
|  | Smoking | Q/F | 4 | X | X | X | X |  |  |
|  | Alcohol | Audit-C | 3 | X | X | X | X |  |  |
|  | Coping | new | 4 | X | X | X | X |  |  |
|  | Daily Diary |  | 10 |  |  |  |  | X |  |
|  | App Use |  | - |  |  |  |  | X |  |
|  | Treatment Feedback | CSQ | 8 |  | X |  |  |  |  |
|  |  | WAI-SR (Focus & HL) | 12 |  | X |  |  |  |  |
|  |  | Strategies (Focus) | 20 |  | X |  |  |  |  |
|  |  | Strategies (HL) | 12 |  |  |  |  |  |  |
|  |  | App | 5 |  | X |  |  |  |  |
|  |  | Home practice |  |  |  |  |  |  |  |
| **Patient Measures** | Demographics | Standard | 10 | X |  |  |  |  |  |
|  | Clinical Characteristics | Standard | - | X | X | X | X |  | X |
|  | Distress | CESD^120^ | 20 | X | X | X | X |  |  |
|  |  | GAD-7^122^ | 8 | X | X | X | X |  |  |
|  |  | Thermometer | 1 | X | X | X | X |  |  |
|  | Mental Health Services | Standard | 1 | X | X | X | X |  |  |
|  | COVID | created | 5 | X | X | X | X |  |  |
|  | Patient Interview | Created (n=~30) | 20 |  |  |  | X |  |  |
| **Patient**  **Healthcare Utilization** | Readmissions | - | - |  | X | X | X |  | X |
|  | Readmissions length | - | - |  | X | X | X |  | X |
|  | Unexpected clinic visits | - | - |  | X | X | X |  | X |

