>.80 to detect a standardized difference between means of 0.56, which can be described as slightly greater than a medium effect size. Aim 1 also hypothesizes that average caregiver burden will be lower in the FOCUS vs HL condition at 2 months. Under the same conditions as above, but with alpha set at .05, it is estimated that power >.80 to detect a standardized difference between means of 0.51, a medium effect size. Power estimates for the hypotheses to be tested in Aim 2 (e.g., patient distress) parallel those for Aim 1. It is possible that fewer patients will agree to participate and the minimum effect sizes will be higher than those for Aim 1 (e.g., if group n’s=50, then effect sizes increase to 0.62 [UC] and 0.57 [HL]).

**Specific Aim 1**: Aim 1 is to evaluate the efficacy of FOCUS when compared to UC and HL on caregiver burden. H1a and H1b: Caregivers in FOCUS will report lower levels of burden 2 months post-treatment than caregivers in UC (H1a) and HL (H1b). The primary predictors of the GEE model are condition (e.g., FOCUS vs UC), time (end of treatment [8 weeks] vs 2 months), and their interaction. The GEE will include as a covariate any baseline measure that differs by group (p<.05) as a potential confound (e.g., age, relationship to patient, baseline burden). Other covariates will be predictors of missing follow-up surveys and/or self-reported burden at 8 weeks or 2 months (p<.05). These covariates will increase the viability of the Missing at Random assumption and improve parameter estimates within a full information maximum likelihood model. As described above, H1a will be assessed at alpha=.025 and H1b at .05. Each hypothesis will be tested using a planned contrast of condition at 2 months assessing the prediction that FOCUS will have a lower mean burden than the comparison condition (UC or HL). A significant main effect for condition would be another indicator of group differences (burden averaged over the 2 assessments).

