Additional analyses will be performed to assess the effect of FOCUS on burden at the 6 month follow- up. A new GEE model will incorporate the three assessments of burden (8 weeks, 2 months, and 6 months) using appropriate covariates. The primary test will be a planned contrast of condition at 6 months. A separate model is justified by 1) the expected increase in missing surveys at 6 months and 2) the expected addition of covariates that predict missing surveys and/or burden at 6 months. This test at the 6-month follow-up will also be conducted for aim 2 outcomes of patient distress and healthcare utilization.

**Specific Aim 2**: Aim 2 is to evaluate the impact of FOCUS on patient health and patient healthcare utilization. H2a and H2b: Patients of caregivers in FOCUS will report lower levels of distress 2 months post- treatment than patients of caregivers in UC (H2a) or HL (H2b). Exploratory: Determine the impact of FOCUS on patient healthcare utilization in the first 2 months and from 3 to 6 months post-treatment (hospital readmissions, length of readmissions, unexpected patient clinic visits). The analysis for this hypothesis parallels that of Aim 1. The main differences are the outcome measure and the sample. If preliminary analyses show that distress exhibits sufficient characteristics to be treated as a continuous variable, then the identity link and linear regression will be used within the GEE. If not, an appropriate link function and regression approach will be applied. The sample of patients has potential to have more missing surveys, to have different predictors of missing surveys, and to have unique predictors of distress. Therefore, these GEE models are likely to have different sets of covariates (e.g., number of serious transplant complications; acute GVHD; relapse).

Similar GEE models will be used to explore group differences in patient healthcare utilization through 2 months and from 3 to 6 months. As noted above, model covariates may differ. The main difference in these models will be driven by the distribution characteristics of the healthcare utilization measures. For those measures that cannot be considered continuous, the link function and regression type within the GEE will be changed to an option that best matches the outcome distribution (e.g., link=binary, regression=logistic for whether or not there were unexpected patient clinic visits).

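### Aim 2 foresees adjusting the patient models for transplant complications, acute GVHD and relapse, which arise after randomisation; if FOCUS alters these events, the adjusted contrast is not the randomised total effect

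*Protocol*

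**What the plan says.** All references are to the protocol; no SAP was available.

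- **Timing.** Under Project Overview and Timeline, dyads are consented at about Day -14 to Day -10, and "The caregiver will then be randomized to FOCUS, HL, or UC". The Randomization paragraph says that dyads "will be randomized at enrollment, to one of the three treatments using balanced-permuted blocks of size six". The background describes the programme "with session 1 occurring prior to transplant, sessions 2-3 taking place immediately following transplant, and sessions 4-6 occurring post-discharge".
- **Covariates for the patient models.** Specific Aim 2 states that "The analysis for this hypothesis parallels that of Aim 1". It adds that the patient sample may have more missing surveys, "to have different predictors of missing surveys, and to have unique predictors of distress", and therefore that "these GEE models are likely to have different sets of covariates (e.g., number of serious transplant complications; acute GVHD; relapse". The healthcare-utilisation models are described as similar, with covariates that may differ.
- **Selection rule carried over from Aim 1.** One sentence limits confounders to baseline measures that differ by group. The next reads: "Other covariates will be predictors of missing follow-up surveys and/or self-reported burden at 8 weeks or 2 months (p<.05". It sets no limit to baseline variables.
- **Availability.** Table 4 schedules patient clinical characteristics at baseline, end of treatment and both follow-ups, so post-baseline values will be on file.
- **Status.** The statistical section places Aims 1 and 2 under the primary analyses, with Holm control. H2a and H2b are directional hypotheses on patient distress at 2 months. Utilisation is exploratory.

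**The concern.** Serious transplant complications and acute GVHD cannot exist at randomisation. Relapse, listed beside them, is most naturally read as relapse after transplant. A covariate that arises after allocation may be affected by it, and a model that conditions on it then estimates a different quantity from the one randomisation protects.

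The protocol's own premises make such an effect plausible. Its background links caregiver burden and distress to worse patient outcomes, including survival. Its design overview expects patient distress and utilisation to be affected both directly and indirectly. Aim 2 is framed as impact on patient health.

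At stake is whether H2a and H2b estimate the total effect of assigning the caregiver to FOCUS. For utilisation the link is closer still, because complications plausibly lead to the readmissions and triage visits that are counted.

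**Working it through.** **1. The plan's own figures.** The stated power above .80 was checked with a two-sided two-sample comparison of means (noncentral t).

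- n=63 per group: 0.56 SD at alpha .025 gives 0.808; 0.51 SD at alpha .05 gives 0.811.
- n=50 per group: 0.62 SD at alpha .025 gives 0.794 (normal approximation 0.805); 0.57 SD at alpha .05 gives 0.806.

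These figures assume no covariates, so restricting the covariates leaves them unchanged.

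**2. Inputs for the size of the problem.** The protocol gives neither an effect of FOCUS on the events nor an association between events and distress. Everything below is assumed.

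**3. Binary event, no shared frailty.** Let the event rate be 0.40 in the comparator and 0.25-0.30 under FOCUS, the event effect on distress 0.5-0.8, and the direct benefit 0.3.

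Mediated part = (rate difference) x (event effect). Total = 0.3 + mediated part. Share lost by adjustment = mediated part / total.

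| Rates | Event effect | Mediated | Total | Lost |
|---|---|---|---|---|
| 40% vs 30% | 0.5 | 0.10 x 0.5 = 0.05 | 0.35 | 14% |
| 40% vs 25% | 0.5 | 0.15 x 0.5 = 0.075 | 0.375 | 20% |
| 40% vs 30% | 0.8 | 0.10 x 0.8 = 0.08 | 0.38 | 21% |
| 40% vs 25% | 0.8 | 0.15 x 0.8 = 0.12 | 0.42 | 29% |

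**4. Standardised event score, with and without shared severity.** Let a be the effect of FOCUS on the score (SD), b the effect of the score on distress, and g the loading of an unmeasured severity factor on both. With within-arm variances of 1, the adjusted coefficient is

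adjusted = total - a x b - a x g².

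The second term is the blocked pathway and the third is the collider term. Both carry the factor a, so both vanish when FOCUS does not change the events. With a total of -0.56 SD:

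| a | b | Adjusted, g=0 | Lost | Adjusted, g=0.4 | Lost |
|---|---|---|---|---|---|
| 0 | 0.3 | -0.56 | 0% | -0.56 | 0% |
| -0.1 | 0.3 | -0.53 | 5% | -0.514 | 8% |
| -0.2 | 0.3 | -0.50 | 11% | -0.468 | 16% |
| -0.3 | 0.5 | -0.41 | 27% | -0.362 | 35% |

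Example (a=-0.2, b=0.3, g=0.4): -0.56 + 0.06 + 0.032 = -0.468. A simulation of 400,000 subjects per setting agrees (-0.467 here), and the model without the event returns about -0.56 throughout.

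**5. Power (n=63, alpha .025).** Without the event, power is about 0.81. With it, power is 0.75 at a=-0.2, b=0.3. At a=0 it rises (0.85 at b=0.3, g=0), because the residual SD shrinks. The main harm is therefore to what is estimated; power may move either way.

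**The case against.** Four points can be made for the plan.

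- **The wording is tentative.** A reader might infer that the protocol commits to this adjustment. It does not: the events are examples of what is likely, and under the parallel Aim 1 rule they enter only if they predict missingness or the outcome at p<.05. This stands. But they are the only examples given for the patient models, and nothing excludes them, so this is a poor choice on the page and not detail left to a SAP.
- **No effect on these events is hypothesised.** Patient distress is measured by CESD and GAD-7 self-report, and GVHD and relapse are not named as targets. A reader might infer that adjustment biases the result in any case, or that shared frailty alone does so. Neither follows: step 4 shows that both terms need FOCUS to change the events. Still, a trial that tests an effect on patient health cannot presuppose that there is none on these events.
- **Missingness.** Sicker patients may well miss surveys, and 30% dropout is planned for. Predictors of missingness are worth using, and simply dropping them from an available-data GEE has its own risk. This too stands, but it does not require them in the outcome model. The statistical section already contemplates multiple imputation, where they can serve as auxiliary variables.
- **Aim 1.** A reader might infer that the burden analysis has the same fault. No post-randomisation covariate is named there, and the examples given for group-difference covariates are baseline ones. The open wording calls for clarification; it is not a demonstrated error.

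**Conclusion.** The point holds in conditional form. The protocol foresees adjusting the Aim 2 patient models for events that follow randomisation. If FOCUS changes those events, H2a, H2b and any utilisation model that carries the same covariates no longer estimate the total randomised effect. If it does not, the linear contrast is unbiased.

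The size cannot be known from the protocol. Under the assumptions of step 3 the loss is 14-29%; with a small effect on the events (a=-0.1, b=0.3) it is 5% without and 8% with shared severity. A larger figure needs a stronger effect of a six-session caregiver programme on these events, for which the protocol offers no evidence.

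This should be fixed, but it is not critical to the trial: the primary outcome, caregiver burden, has no such covariate named, and utilisation is exploratory.

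**What to change.** Replace the parenthetical examples in Specific Aim 2 with wording such as:

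> Covariates in the patient outcome models are restricted to variables measured before randomisation, including the baseline value of the outcome, the caregiver gender stratum and named pre-transplant disease characteristics. Serious transplant complications, acute GVHD and relapse are reported by arm. They are used only as auxiliary variables in multiple imputation, or in a sensitivity or mediation analysis labelled as such.

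Make the two changes together, so that information on missingness moves to the imputation and is not lost. Apply the same restriction to the utilisation models. As a clarification in Specific Aim 1, state that predictors of missingness or burden entered in the outcome model are baseline variables. Settle this before outcomes are compared by arm.

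Cost: wording, no new data and no change to sample size or stated detectable effects. There is a little more analysis work for the imputation, and some reduction in residual variance is given up. In the a=0, b=0.3, g=0 setting, for instance, adjustment would have lowered the residual SD from 1 to about 0.95.

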**Assessment Visits.** After informed consent, caregivers will complete a battery of baseline questionnaires and a hair sample will be collected for cortisol testing (100% of caregivers allowed us to take hair samples during the pilot study). We anticipate this process taking about 30-40 minutes for the caregivers to complete. After completing questionnaires, caregivers will schedule their 6 treatment visits. Patients will complete a brief demographic questionnaire and three measures to assess distress. This should take about 10 minutes for patients to complete.

The same assessments will be completed at baseline, end of treatment (~8 week post baseline), and at follow-ups. Hair samples will be collected again from caregivers at the 6-month assessment. Whenever possible, assessment visits will coincide with a clinic visit to decrease burden. As needed, questionnaires will be mailed, texted (link) or emailed to participants (e.g., 6-month visit). Caregivers will be compensated $25 for baseline, end of treatment, and the 2-month follow-up visits; they will be paid $50 for the 6-month follow-up. Patients will be compensated $20 at each assessment time point (4 total). As described in Section C.5.5., caregivers will be asked to complete a daily diary each evening that should take no more than 2 minutes to complete. Caregivers who complete at least 70% of daily diary questions will receive a bonus payment of $40 at the end of treatment assessment visit.

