**Aim 2 Patient Healthcare Utilization Outcomes**. Healthcare utilization will be assessed by extracting the following from patient charts: readmissions to the hospital, length of stay of all hospital readmissions, and unexpected clinic visits post-discharge. Unexpected clinic visits post-discharge will be a secondary measure of healthcare utilization. These visits will be captured when patients are scheduled as a “triage” visit, as all triage visits are considered unexpected when documented in this manner in the clinic. At the 6 month follow-up assessment, healthcare utilization outcomes will be extracted from the chart when possible, but self-report and supplementation with outside records will also be done in cases when the caregiver/patient is no longer being seen at Moffitt (e.g., moved back home).

Additional Caregiver Variables (mechanisms, moderators, possible covariates). Stress and affect will be captured by self-report and biomarker data (cortisol). The Perceived Stress Scale (PSS) assesses one’s perception of life as unpredictable, uncontrollable, and overwhelming on a 5-point Likert scale.131 The Impact of Events Scale Revised (IES) assesses intrusion, arousal, and avoidance symptoms around the diagnosis of cancer on a 5-point Likert scale. The Positive and Negative Affect Schedule (PANAS) assesses broad levels of positive and negative affect (e.g., determined, nervous) on a 5-point Likert scale.136The National Comprehensive Cancer Network Distress Thermometer will be used as a 1-item measure of overall (non-specific) distress in the past week.

Hair samples will be collected at baseline and the 6 month follow-up to measure cortisol concentrations from the prior month.137-139 Our consultant, an expert in the measurement of hair cortisol concentrations as a biomarker for assessing long-term activity of the hypothalamic-pituitary-adrenocortical (HPA) axis and chronic stress, will aid in the collection, analysis, and interpretation of the cortisol results (see LOS). Baseline hair samples will be collected by study staff; 6 month samples will be collected by the caregiver and mailed to the study team (detailed instructions will be provided to caregivers for collection). We chose hair (instead of saliva, for instance) primarily due to the ease of data collection, all while being able to accurately collect our construct of interest (e.g., saliva often requires collection multiple times per day over a series of days).

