# STATISTICAL CONSIDERATIONS

### Data Management and Statistical Considerations

Descriptive statistics will be used to summarize and evaluate the distributions of all study variables. Transformations will be applied, as needed, prior to hypothesis testing. Missing data analyses will assess 1) prospective predictors of missingness that may influence interpretation and generalizability of results from hypothesis testing and 2) whether or not multiple imputation for managing missing data would be beneficial. Paired comparisons will be used to identify group differences, despite randomization, in demographics, clinical, and psycho-social variables that will then be included as covariates when testing hypotheses. Primary analyses for Aims 1 and 2 will use generalized estimating equations (GEE) with an identity link function, linear regression, and compound symmetry for the working correlation matrix. Advantages to using GEE, which fit population-averaged models, are to 1) assess changes in the outcome variable over time, 2) aggregate measures of the outcome variable across time to capture condition differences that may appear at different times for different participants, 3) assess primary hypotheses with targeted comparisons that incorporate data from all participants across multiple assessments, and 4) help effectively manage missing data by study completers under the missing at random assumption (MAR). The Holm method148 will be applied to control for experiment-wise error in the primary analyses, with alpha set at .025 for tests of FOCUS vs UC and set at .05 for FOCUS vs HL. Primary analyses will be performed using SAS version 9.4 (SAS Institute, Cary, NC).

**Power Estimates**: There will be 90 dyads randomized to each condition, with at least 63 per condition (30% dropout) expected at the 2-month assessment. PASS 16 was used to estimate power and effect size based on this sample size. Aim 1 hypothesizes that average caregiver burden will be lower in the FOCUS vs UC condition at 2 months. With alpha=.025, a two-sided test, and group n’s of 63, it is estimated that power

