**Specific Aim 3**: Aim 3 is to evaluate putative mechanisms and moderators of FOCUS. Prospective mechanisms of lower perceived burden are higher mindfulness and self-efficacy, and lower stress and negative affect. The measure of these variables at 2 months (6 months for cortisol) post-treatment will be evaluated using the same approach described for the analyses in Aim 1.

These variables will also be assessed within the daily diary component of the study, which allows for 2 additional opportunities to assess mechanisms. First, the repeated, daily measures will be assessed using GEE for condition comparison with an emphasis on the main effect of condition (averaged over the multiple daily measures) and the condition x time interaction (diverging trajectories with the group differences increasing over time). Second, the repeated, daily measures of an active mechanism variable and the measures of burden at 8 weeks and 2 months will be entered into a structural equation model designed to evaluate whether or not changes in an active mechanism variable precede changes in burden. Mplus version

8.4 will be used for these models.149

Potential moderators (e.g., gender, age, relationship to patient, income, proximity to cancer center [defined as the mileage of home residence from Moffitt], baseline caregiver distress) of FOCUS on caregiver burden will be evaluated by adding to the GEE model for Aim 1 the moderator (e.g., gender) and its interaction with condition. A significant interaction will be further explored by testing differences in burden for each condition within appropriate subsets of the moderator (e.g., male and female).

**Data management**. Study data will be managed through REDCap (Research Electronic Data Capture), a data management software system supported and provided free by Moffitt. REDCap allows creation of customized, secure data management systems including web-based data entry forms, reporting tools, and a full array of security features including user and group-based privileges with a full audit trail of data manipulation and export procedures. Nationally, REDCap software is developed, enhanced, and supported through a multi- institutional consortium led by Vanderbilt University. The Project Manager, along with the Research Coordinator, will oversee creation of the database, questionnaires, and an automated messaging system.

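### Hair cortisol has one post-baseline sample, so the Aim 1 repeated-measures model assigned to it cannot be fitted as written; the 6-month contrast needs its own stated model

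*Protocol*

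**What the plan says.** **Sampling.** The Additional Caregiver Variables text states: "Hair samples will be collected at baseline and the 6 month follow-up to measure cortisol concentrations from the prior month". Assessment Visits agrees: "Hair samples will be collected again from caregivers at the 6-month assessment". Table 4 marks cortisol at baseline and Follow-up 2 only, with nothing at end of treatment or Follow-up 1.

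**Analysis of cortisol.** Specific Aim 3 states: "The measure of these variables at 2 months (6 months for cortisol) post-treatment will be evaluated using the same approach described for the analyses", with Aim 1 named as the source. For cortisol it changes only the time point.

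**The Aim 1 approach.** Specific Aim 1 gives the main predictors as "condition (e.g., FOCUS vs UC), time (end of treatment [8 weeks] vs 2 months), and their interaction". To this, the general statistical section adds "compound symmetry for the working correlation matrix". The Aim 1 test is a planned contrast of condition at 2 months. A second Aim 1 model, for 6 months, uses three post-baseline assessments (8 weeks, 2 months and 6 months).

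**Covariates.** Specific Aim 1 admits a baseline measure if the groups differ on it at p<.05. It also admits predictors, again at p<.05, of missing follow-up surveys or of self-reported burden at 8 weeks or 2 months. Randomization is stratified by caregiver gender, but gender is not named as a fixed covariate.

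**Timing in the aims.** The opening statement of Aim 3 puts hair cortisol in a list of mechanism measures that it describes as collected by daily diary and at the 2-month assessment.

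**The concern.** The protocol makes a positive statement about how cortisol will be analyzed, and the model it points to does not fit the data that will be collected. Both Aim 1 models, for 2 months and for 6 months, need at least two post-baseline values per person, and cortisol supplies one. This is a wrong cross-reference in the document itself, not a detail left for a statistical analysis plan.

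Whoever runs the analysis must therefore decide which terms to drop and how to use the baseline sample, possibly with the data in hand. Cortisol is the only biological mechanism measure in Table 4, and the protocol presents the biomarker data as a novel part of the project. The cortisol comparison also falls at the visit where the protocol expects more missing data, so a covariate that is already collected should not be left to chance.

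**Working it through.** **1. The plan's own power figures, for scale.** Inputs from Power Estimates are 90 randomized per arm and 30% dropout, so 270 × 0.7 = 189, or 63 per arm. Two-sided two-sample t power is then:
- FOCUS vs UC, d = 0.56, alpha .025: 0.808 (normal approximation 0.816).
- FOCUS vs HL, d = 0.51, alpha .05: 0.811 (normal approximation 0.817).

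Both agree with the stated power above .80. These figures are for the 2-month assessment. The protocol gives none for cortisol and no 6-month hair-return rate. If 63, 54 or 45 usable samples per arm are assumed (30%, 40% or 50% loss), the difference detectable with 80% power is:
- alpha .025: 0.555, 0.600 and 0.659 SD.
- alpha .05: 0.503, 0.544 and 0.597 SD.

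**2. Can the Aim 1 mean model be fitted to cortisol?** With three arms the columns are an intercept, two condition indicators, one time indicator and two condition-by-time products: 1 + 2 + 1 + 2 = 6.
- Two post-baseline times, 63 per arm: 378 rows, rank 6 of 6. This is the burden model.
- One post-baseline time, 63 per arm: 189 rows, rank 3 of 6. The time column is constant and so repeats the intercept, and each product column repeats its condition column.

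The three-assessment Aim 1 model has 1 + 2 + 2 + 4 = 9 columns. With data at only one of its times, its rank is also 3.

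**3. The working correlation.** Compound symmetry has one parameter, the correlation between two values from the same person. With one post-baseline value per person there are no pairs from which to estimate it.

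**4. What survives.** An intercept and two condition terms have rank 3 and fit. In a simulated data set with one record per person, GEE standard errors were identical to those from ordinary regression with robust standard errors. Both contrasts, FOCUS vs UC and FOCUS vs HL at 6 months, remain estimable.

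**5. The use of baseline cortisol.** The screening rule offers two routes.
- *Group imbalance at p<.05.* Under randomization any one comparison meets this by chance about 5% of the time.
- *Prediction of missing surveys or of burden.* Read literally, this does not mention cortisol as the outcome. If it is carried over as prediction of 6-month cortisol, then t = r√(n − 2)/√(1 − r²). At r = 0.3 and n = 189, t = 0.3 × √187/√0.91 ≈ 4.3. At n = 135 (45 per arm), t ≈ 3.6. Baseline cortisol would then normally enter.

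**6. What fixed adjustment is worth.** The baseline-to-6-month correlation r is not in the document, so 0.3 to 0.6 is an assumption. The residual variance factor is 1 − r², the equivalent sample is 63/(1 − r²), and the detectable difference scales by √(1 − r²).

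| r | 1 − r² | Equivalent n per arm | 0.51 becomes |
|---|---|---|---|
| 0.3 | 0.91 | 69 | 0.49 |
| 0.5 | 0.75 | 84 | 0.44 |
| 0.6 | 0.64 | 98 | 0.41 |

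The comparison is with no baseline adjustment at all. It uses the 2-month count of 63, so the sample sizes are illustrative. The proportional reduction in variance does not depend on that count.

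**7. The 2-month statement.** The opening Aim 3 text associates hair cortisol with the 2-month assessment. Assessment Visits, Additional Caregiver Variables, Table 4 and the parenthesis in Specific Aim 3 all place it at 6 months.

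**The case against.** The strongest reply is that the test that matters is unaffected. Aim 1 is decided by a contrast of condition at a stated visit, and the parenthesis on cortisol moves that contrast to 6 months. With one value per person the GEE reduces to linear regression, which any analyst would see. This stands in part: the contrast can be estimated, and some adaptation was evidently intended. A reader might infer that cortisol has no estimable model, and the documents do not support that. The text still names terms and a correlation that cannot exist for this measure, and it does not say what replaces them.

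A second reply is that the screening rule would usually bring baseline cortisol in. This also stands, if the rule is translated to cortisol as the outcome, and it limits the precision gain. The literal wording refers to burden, however, and entry still depends on a test result.

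A third reply is that the general section already allows transformations as needed, and that further detail can go into a statistical analysis plan. That is true of the transformation. It does not cure a statement in the protocol that points to the wrong model.

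Three stronger readings are tempting and should not be drawn:
- *Baseline as a time level would halve the condition effect.* Every time level in the Aim 1 models is post-baseline, and nothing in the plan enters baseline as one.
- *The change of collector biases the comparison.* The protocol says "Baseline hair samples will be collected by study staff" and "6 month samples will be collected by the caregiver and mailed to the study team". The 6-month method is the same in all arms, so it does not by itself bias the randomized contrast. The protocol also notes that most participants have gone home by then and provides detailed instructions.
- *Steroid use or hair treatment goes unrecorded.* This argues from silence, because neither the demographic items nor the collection instructions are fully itemized. The importance of these factors would also have to come from outside the documents.

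**Conclusion.** The point holds in limited form. The Aim 1 GEE cannot be fitted to cortisol as written: three of its six mean parameters (time and the two interaction terms) and the working correlation are not estimable from one post-baseline value. The 6-month condition contrast is estimable, so this is a faulty specification and not an impossible analysis. The opening Aim 3 statement also implies a 2-month cortisol value that no part of the schedule provides.

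The benefit of always adjusting for baseline cortisol is at most a 9% to 36% reduction in residual variance, for an assumed correlation of 0.3 to 0.6 and a linear relation. It will be smaller, possibly nil, wherever the screening rule would have admitted baseline cortisol anyway. The rank result rests only on the sampling schedule and needs no assumption.

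The defect concerns one Aim 3 mechanism measure. It does not touch the primary burden analysis, and stress is also measured by questionnaire. It should still be corrected, because the sentence cannot be carried out as it stands.

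**What to change.** In Specific Aim 3, take cortisol out of the cross-reference to Aim 1 and add: *Hair cortisol at 6 months (log-transformed if needed) will be compared between conditions by linear regression with baseline cortisol and caregiver gender as prespecified covariates; no time terms.*

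In the opening Aim 3 statement, say that hair cortisol is assessed at 6 months, and keep the diary and 2-month timing for the other measures.

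The cost is wording in the protocol, carried into the statistical analysis plan if there is one. Baseline cortisol and gender are already collected, so no new samples, visits, survey items or staff are needed. Hair collection stays as planned.
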